## Abstract

**Introduction:**

Pain is the main symptom of osteoarthritis (OA) with approximately 50% of patients reporting moderate-to-severe pain. Total knee replacement (TKR) is the ultimate treatment option to alleviate pain in knee OA. Nevertheless, TKR does not provide complete relief for all as approximately 20% of patients experience chronic postoperative pain. Painful peripheral stimuli may alter the central nociceptive pathways leading to central sensitisation that can influence treatment response in patients with OA. Currently, there is no objective protocol for detecting whether a patient will respond to a given treatment. Therefore, there is a need for a better mechanistic understanding of individual factors affecting pain relief, consequently informing personalised treatment guidelines. The purpose of this research is to examine the feasibility of conducting a full-scale mechanistic clinical trial in painful knee OA investigating the analgesic response to intra-articular bupivacaine between those with or without evidence of central sensitisation.

**Methods and analysis:**

The Understanding Pain mechanisms in KNEE osteoarthritis (UP-KNEE) study is a feasibility, double-blinded, placebo-controlled randomised parallel study in participants with radiographically defined knee OA and with self-reported chronic knee pain. The study involves the following assessments: (1) a suite of psychometric questionnaires; (2) quantitative sensory testing; (3) magnetic resonance imaging (MRI) scan of the knee and brain; (4) a 6-minute walk test; and (5) an intra-articular injection of bupivacaine or placebo (sodium chloride 0.9%) into the index knee. Assessments will be repeated post intra-articular injection apart from the MRI scan of the knee. Our aim is to provide proof of concept and descriptive statistics to power a future mechanistic trial.

**Ethics and dissemination:**

Ethical approval was obtained from the Health Research Authority (HRA) (REC: 20/EM/0287). Results will be disseminated via peer-reviewed journals and scientific conferences. The results will also be shared with lay audiences through relevant channels, such as Pain Centre Versus Arthritis website and patient advocacy groups.

**Trial registration number:**

NCT05561010.

STRENGTHS AND LIMITATIONS OF THIS STUDYThe study attempts to address a knowledge gap by providing mechanistic understanding of the factors contributing to the individual pain relief in knee osteoarthritis.The feasibility design will support a future main trial.Patients were involved in the development of the study protocol. They helped to identify the most relevant outcome measures, which were reordered to prioritise the patients’ preferences.Owing to the nature of the feasibility study, no formal hypothesis testing will be performed in this trial. It will provide descriptive statistics which will inform the design and sample size requirements of a future definitive mechanistic trial.

## Introduction

### Rationale

Knee osteoarthritis (OA) is a leading cause of pain, functional disability and is a substantial economic burden on society and healthcare systems.^1–3^ Treatment guidelines for chronic knee pain in OA are mainly focused on pain management with a combination of pharmacological and non-pharmacological treatment approaches, but no disease-modifying treatment currently exists.^4^ Total knee replacement (TKR) is the ultimate treatment to alleviate pain, nevertheless chronic pain is still reported in about 20% of patients after the surgery.^5^ Currently, there is no objective protocol to detect how a patient will respond to a given OA treatment. Moreover, there is also a poor correlation between the severity of joint damage and severity of pain,^6^ which points to the contribution of central pain mechanisms.

Painful peripheral stimuli may alter the central nociceptive pathways leading to central sensitisation that can influence treatment response in patients with OA.^7^ Sensitisation, which plays a key role in augmenting OA pain, is defined as a modified perception of pain due to increased impulses from the peripheral nervous system (peripheral sensitisation) along with augmentation of pain signals in the central nervous system (central sensitisation).^8^ Central sensitisation was estimated to be present in about 30% of patients with OA^9^ and was found to be a predictor for developing chronic postoperative pain after TKR.^10 11^

Validated proxies, including questionnaires, neuroimaging and quantitative sensory testing (QST), have been used to examine pain sensitisation. However, a gold standard to diagnose pain sensitisation in a clinical setting is lacking, and individualised mechanism-based treatment in knee OA remains a pressing need.

### Evidence gap

Given the necessity for better understanding of the mechanisms of pain relief in knee OA, the purpose of this research is to examine the feasibility of conducting a full-scale mechanistic clinical trial investigating the analgesic response in knee OA between those with or without evidence of central sensitisation. The use of intra-articular bupivacaine, as an experimental medicine approach, has been shown to significantly reduce knee pain 1 hour after injection in previous studies^12 13^; as it temporarily blocks peripheral pain stimuli, thereby potentially unmasking central pain components. Given that peripheral input commonly triggers central sensitisation, the theory that local anaesthesia will assist in differentiating patients with centrally mediated pain mechanisms is also supported by the notion that regional anaesthesia or local anaesthesia can reduce the risk of persistent postoperative pain 6 months after surgery according to a previous systematic review and meta-analysis.^14^ Additionally, the use of comprehensive pain phenotyping tools including MRI of the knee and brain will enable a better mechanistic understanding of individual factors affecting pain relief, consequently informing future personalised treatment guidelines.

### Objectives

The primary objective of the UP-KNEE study is to evaluate the feasibility of a main definitive trial by:collecting data to inform sample size calculation;testing the recruitment process;Timing of the outcome measures;Testing the robustness of randomisation;Testing the integrity of the research protocol; andqualitative assessment of the acceptability of the methods of the feasibility study.The secondary objective of the study is to explore correlations of the analgesic response with indicators of central and peripheral pain mechanisms derived from MRI of the brain and knee, questionnaires and QST.

### Hypothesis

For the future main trial, the hypothesis is that the analgesic response to a peripherally targeted intervention aiming to reduce knee pain will reveal two groups. The non-responders group will be patients with predominantly centrally driven pain characteristics, who will show less analgesic response to the peripherally targeted intervention while the responders group will be patients with predominantly peripheral pain who will show a greater analgesic response to the peripherally targeted intervention. Both groups will respond similarly to placebo. However, this feasibility study is not intended to test the hypothesis of the main trial.

## Methods and analysis

### Study design

The study will be a feasibility, double-blinded, placebo-controlled randomised parallel study in participants with radiographically defined knee OA and with self-reported chronic knee pain. The study design was guided by the recommendations of the Consolidated Standards of Reporting Trials (CONSORT) 2010 statement extension to randomised pilot and feasibility trials.^15^ The study protocol has been reported in accordance with the Standard Protocol Items: Recommendations for Interventional Trials (SPIRIT) guidelines (online supplemental file A).^16^

10.1136/bmjopen-2023-072138.supp1Supplementary data

### Study setting

This is a single-centre study. The study activities will be carried out at the Sir Peter Mansfield Imaging Centre, University of Nottingham.

### Sample size

This is a feasibility study aiming to provide first proof of concept and descriptive statistics to power a future diagnostic trial. We aim to recruit 50 participants (25 to each group). This would be a large enough sample to assess the feasibility and inform a main trial based on statistical methodological papers providing recommendations about sample size requirements for feasibility and pilot studies.^17–19^

### Eligibility criteria

The inclusion criteria are; patients aged 45 years and older who have the capacity to give informed consent and have radiographically defined OA knee changes (Kellgren and Lawrence Grading System K/L>2/4) with knee pain, particularly self-reported knee pain at the most severely affected side measuring between 30 and 80 mm on a 100 mm Visual Analogue Scale (VAS) for rest, use or night pain and being able to perform the 6-minute walk test (6MWT). The VAS anchors are: 0 as ‘no pain’ and 100 as ‘the worst pain imaginable’.

The exclusion criteria are; patients having major medical, neurological and psychiatric comorbidities that would preclude completion of the study protocol. Patients who have a diagnosis of OA in any joint other than the knee with pain VAS≥30 mm, fibromyalgia, systemic or local knee infection, severe coagulopathy or taking anticoagulant therapy, known hypersensitivity to bupivacaine, taking neuropathic pain medications for their OA-related pain such as strong opioid analgesics and antiepileptic drugs will also be excluded. Known contraindications for MRI are also exclusion criteria.

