### Outcomes

#### Primary outcome measures

The change in pain score using a 100 mm VAS during the 6MWT from baseline to 1 hour after intra-articular injection with bupivacaine or placebo.The change in pain score using the VAS at rest from baseline to 1 hour after intra-articular injection with bupivacaine or placebo.

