### Statistical methods

Considering the feasibility nature of the study, no formal hypothesis tests will be performed to statistically compare the two study arms and descriptive statistics will be presented. Appropriate parametric or non-parametric statistics will be used according to the data characteristics.Summary statistics will be used to evaluate feasibility objectives such as the feasibility to recruit, timing measurements, to describe the sample and to inform the future main trial by providing power and sample size calculation. Participant acceptability feedback will be qualitatively synthesised using thematic analysis.Primary and secondary outcomes will be descriptively summarised by group as follows:Correlations between the change of pain score and QST measurements at baseline and after intra-articular injection with bupivacaine or placebo.Correlations between the change of pain score and brain network activity at baseline and after intra-articular injection with bupivacaine or placebo using predefined seeds in the pain processing regions.Correlations between the change of pain score and the level of joint damage quantified by MOAKS and measured at baseline.Estimates of between-group effect will be reported as estimates with 95% CIs without p values.In view of the exploratory nature of the study, missing data will not be imputed. The proportion of missing data for each outcome will be described.Differences in effects will be reported descriptively for primary and secondary outcomes between the following subgroups:Based on the stratification variable according to CAP-Knee Questionnaire scores with respect to whether pain is predominantly centrally or peripherally driven.The patients will be divided into responders and non-responders based on a cut-off value of ≥17 mm reduction in VAS post injection.^39^

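### Patients can enter on use or night pain alone, so anyone starting below 17 mm on the VAS used for the responder split is a non-responder by arithmetic under either injection

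*Protocol article*

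**What the plan says.** Under Eligibility criteria, the most severely affected knee must have pain "measuring between 30 and 80 mm on a 100 mm Visual Analogue Scale (VAS) for rest, use or night pain". The scale is anchored at 0 for no pain. Read plainly, any one of the three pain types qualifies a patient, and no separate minimum for rest pain appears anywhere in the article.

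Primary outcome measures lists two outcomes: "The change in pain score using a 100 mm VAS during the 6MWT from baseline to 1 hour after intra-articular injection", and "The change in pain score using the VAS at rest from baseline to 1 hour after intra-articular injection with bupivacaine or placebo".

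Statistical methods says that patients will be "divided into responders and non-responders based on a cut-off value of ≥17 mm reduction in VAS post injection", and that differences in effects on the primary and secondary outcomes will be described between these subgroups. It does not say whether the cut-off applies to the 6MWT VAS, the rest VAS or both. Randomisation is stratified on the CAP-Knee score only.

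For the future main trial, the Hypothesis section states that "The non-responders group will be patients with predominantly centrally driven pain characteristics". It adds that the present study is not meant to test this.

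**The concern.** Entry rule, outcome and cut-off fit badly together. A patient who qualifies on use or night pain may have a rest VAS anywhere down to 0. If the cut-off is applied to rest VAS, a patient starting below 17 mm is a non-responder before the injection is given, whatever it contains. The non-responder subgroup then holds two kinds of patient: those who had room to improve by 17 mm and did not, and those who had no such room. Only the first kind says anything about analgesic response. Because the article compares responders with non-responders on the primary and secondary outcomes, the mixture carries into those comparisons.

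The unnamed VAS adds to this. One patient can be a responder on the 6MWT VAS and, because of the floor, a non-responder on rest VAS.

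**Working it through.** **The plan's own figure.** The target of 50 (25 per group) rests on cited methodological papers, with no alpha, power, effect or SD. There is nothing to reproduce, and the sample size is not disputed.

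**Floor.** Largest possible reduction = baseline score. Baselines of 0, 5, 10 and 16 mm allow reductions of at most 0, 5, 10 and 16 mm, so none reaches 17 mm. At 17 mm only complete relief counts. Under an assumed 50% relief, the baseline must be at least 17/0.5 = 34 mm.

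**How many patients.** The article gives no baseline rest VAS. Assume a normal distribution with parameters m and SD, truncated at 0. The share below 17 mm is [Φ((17−m)/SD) − Φ(−m/SD)] / [1 − Φ(−m/SD)].

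| m (mm) | SD 15 | SD 20 | of 50 |
|---|---|---|---|
| 20 | 36% | 33% | 18 or 17 |
| 30 | 17% | 20% | 9 or 10 |
| 40 | 6% | 10% | 3 or 5 |

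Here m is the value before truncation; for m = 20 the actual mean is about 23 mm (SD 15) or 26 mm (SD 20). The model also ignores the requirement of 30 to 80 mm on at least one pain type. It gives a range, not an estimate.

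**Make-up of the non-responder group, if rest VAS is used.** Let f be the share below 17 mm. Assume that, among patients able to respond, 60% do so on bupivacaine and 30% on placebo, a mean of 45% with equal arms. Floor cases then form f / [f + 0.55(1−f)] of all non-responders:
- f = 6%: 0.06/0.577 = 10%
- f = 20%: 0.20/0.640 = 31%
- f = 36%: 0.36/0.712 = 51%

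The highest attainable responder rate is 1−f. At f = 20% the assumed rates of 60% and 30% become 48% and 24%, so the difference falls from 30 to 24 percentage points.

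**Rest VAS as a continuous outcome.** Assume baselines of 8 mm (low rest pain) and 45 mm (others), and relief of 50% versus 25%. The between-arm difference is 0.25 × [45(1−f) + 8f]. This is 11.25 mm at f = 0 and 9.4 mm at f = 20%. At an assumed SD of 20 mm, two-sided 5% and 80% power, these need 50 and 72 per arm.

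The 9.4 mm is the right figure for a main trial that enrols the same mixture. If that trial were planned on 11.25 mm with 50 per arm, z = 9.4/(20√(2/50)) = 2.35, and power would be about Φ(2.35 − 1.96) = 65%.

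**The case against.** The strongest reply is that this is a descriptive feasibility study with no tests, that both arms face the same floor, and that the choice of scale for one subgroup may be settled in the full protocol or analysis plan. Much of this stands, and it rules out several stronger readings that a reader might infer.

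- *Patients with little rest pain cannot improve.* This is true only at 0 mm. From 1 to 16 mm they can improve by up to their baseline score, but cannot reach 17 mm.
- *The rest-VAS effect and SD are wrong for planning.* They are not. The between-arm estimate is valid for the population enrolled and suits a main trial with the same entry criteria. Learning that rest VAS has a floor is itself a feasibility result.
- *Patients missing 17 mm will be labelled centrally driven.* That hypothesis belongs to the main trial. In this study, CAP-Knee score separates central from peripheral pain, both for stratification and as its own subgroup. Nor do the documents say that movement-related pain is the peripheral type.
- *The cut-off is meant for rest VAS, or should be moved to 6MWT VAS.* The article says neither, and preferring one scale is a judgement it does not support.

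The classification problem does not go away. An absolute cut-off with no baseline condition is a stated rule. Whichever VAS it uses, a patient below 17 mm on that scale is a non-responder by arithmetic. If only 6MWT VAS was intended, the rest-VAS responder problem falls away, but the cap on change in the rest-VAS primary outcome remains.

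**Conclusion.** The point holds as a fault in the responder classification. Patients with a pre-injection value below 17 mm on the VAS used cannot be responders under either treatment, and counting them as non-responders mixes low baseline pain with lack of analgesic response. The scale floor and the plain reading of the entry rule are enough to establish this.

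The size is assumed throughout: roughly 3 to 18 of 50 patients on rest VAS under the distributions shown. No comparable range is offered for 6MWT VAS. Type I error and power in this study are not affected, since nothing is tested. The between-arm rest-VAS estimate is not shown to be biased.

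**What to change.** In the analysis wording:

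1. Name the VAS used for the 17 mm split: 6MWT, rest, or each separately.
2. Classify only patients whose pre-injection value on that scale is at least 17 mm. This conditions on a value measured before treatment, so treatment cannot affect it.
3. Report the number below 17 mm by arm. Baseline rest pain is not a stratification factor, so these patients may fall unevenly between arms.
4. Report the rest-VAS effect and SD overall, as the planning figures for a main trial with the same entry criteria. Add the same figures for patients with baseline rest VAS of at least 30 mm as a supplement, to be used for planning only if the main trial sets that rest-pain minimum.

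Eligibility, recruitment and procedures stay as they are. The cost is a smaller denominator for the responder split. Patients only just above 17 mm will still need near-complete relief to count as responders, so the restriction removes the impossible cases but not all dependence on baseline.

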### Recruitment

The trial flow is summarised in figure 1. Eligible participants will be recruited mainly through the secondary care pathway at the Trauma and Orthopaedic department in Nottingham University Hospitals (NUH) National Health Service (NHS) Trust. The clinical team directly involved in patient care will identify participants as part of their routine clinical review. In addition, there are other potential methods of patient recruitment to the UP-KNEE study, such as Primary Care pathways and participants who have previously participated in previous research in the Pain Centre Versus Arthritis and gave consent to be contacted again regarding future studies.

**Figure 1 F1:**
[figure not shown]
Overall trial flow. fMRI, functional MRI; GP, general practice, OA, osteoarthritis; PIS, participant information sheet; QMC, Queen’s Medical Centre; QST, quantitative sensory testing; SPMIC, Sir Peter Mansfield Imaging Centre; TKR, total knee replacement.

Informed, written consent will be obtained prior to any research activities (online supplemental file B). The participant will be given the opportunity to choose whether they consent via phone or at the appointment. Verbal consent will be taken in accordance with NUH verbal consenting guidance. Participants can withdraw from the study at any timepoint. In the event of their withdrawal, data already collected will be used, but no further data will be acquired.

10.1136/bmjopen-2023-072138.supp2Supplementary data

### Randomisation procedure and concealment of allocation

Eligible participants will be randomised in a 1:1 allocation ratio. An online computer service (SealedEnvelope.com) will be used for stratified randomisation to either intra-articular injection of bupivacaine or sodium chloride 0.9%. This facility generates codes that are concealed from the research team to either group. To mitigate against risk of allocation imbalance with respect to whether pain is predominantly centrally or peripherally driven, stratification will be based on the scores of the Central Aspects of Pain in the Knee (CAP-Knee) questionnaire, which will be sent to participants before the research visit. Participants will be randomised on a 1:1 allocation basis to either bupivacaine or placebo. To ensure blinding of the investigators to the participant’s group assignment, an authorised research nurse will prepare the allocated treatment. The randomisation schedule will be embedded by the research nurse in a secure password-protected folder to achieve allocation concealment.

### Blinding

Investigators and participants will be blind to the treatment allocation. To reduce the risk of interpretation bias, investigators analysing the data will also be blinded to the treatment allocation, and any manual image analysis will be performed by an investigator blinded to clinical status.

Emergency unblinding will only be done if emergencies occur that can be directly linked to the study medication, where it is essential to know if the patient was actually given bupivacaine.

### Experimental procedures

The study involves a single visit in which data will be collected. As per the study protocol (V.1.6, 26 January 2023), the interventions will include an assessment to check patients’ suitability to undergo intervention with a local anaesthetic (bupivacaine) or placebo (sodium chloride 0.9%) intra-articular knee injection. During the visit, all participants will be invited to undertake the following assessments: (1) complete health questionnaires; (2) undergo QST; (3) MRI scan of the knee and brain; (4) perform a 6MWT; and (5) participants will then receive an intra-articular injection of bupivacaine or placebo into the index knee. Assessments will be repeated post intra-articular injection apart from the MRI scan of the knee.

Online supplemental file C contains a detailed description of the study intervention, written in accordance with the Template for Intervention Description and Replication (TIDieR) checklist and guide.^20^

10.1136/bmjopen-2023-072138.supp3Supplementary data

The timings of the postinjection assessments were chosen based on the impact of the timing of bupivacaine administration on its analgesic effects. As the time to peak concentration is 43.4±23.1 min based on previous research using bupivacaine for peripheral analgesia,^21^ there will be a 20 min interval post injection to ensure sufficient time to demonstrate the full effect of local anaesthesia and for the postprocedural care. The postinjection procedures will then be completed between 20 and 60 min post injection.

